**Table 3: Study visits and electronic case report forms (Appendix H)**

| eCRF                | Visit | Enrollment & Baseline | Procedure | Discharge | 1-3M | 6M Phone Visit | 12M | 24M Phone Visit | Interim Follow-up |
|---------------------|-------|-----------------------|-----------|-----------|------|----------------|-----|-----------------|-------------------|
| Baseline            |       | X                     |           |           |      |                |     |                 |                   |
| Inclusion/Exclusion |       | X                     |           |           |      |                |     |                 |                   |
| Procedure           |       |                       | X         |           |      |                |     |                 |                   |
| Follow Up           |       |                       |           | X         | X    | X              | X   | X               | X*                |
| Medication          |       | X                     | X         | X         | X    | X              | X   | X               | X                 |
| Protocol Deviation  |       | X**                   | X         | X         | X    | X              | X   | X               | X                 |

\*Complete if stroke or TIA is confirmed

\*\* Complete if informed consent/informed consent form was not appropriately obtained/completed, visit out of window, test not completed.

Additional eCRFs, reports and assessment noted below should be completed upon occurrence, and/or as applicable:

- Withdrawal eCRF
- Adverse Event eCRF
- Protocol Deviation eCRF
- Death eCRF
- Follow-up eCRF for interim/unscheduled visits
- Modified Rankin Scale (**Appendix J**) (complete 90 days after confirmed stroke /TIA)

If a suspected stroke/TIA has occurred, the subject should be seen by a stroke/TIA neurologist for evaluation and appropriate neurological testing (i.e. CT or MRI, and CTA or MRA). If a stroke or TIA is confirmed, a TOE is required as soon as possible to confirm device placement, LAA flow parameters and presence/absence of device-related thrombus. See Section 8.1 for further details.

## 6.1 Screening/Enrollment/Baseline

The following baseline and enrollment activities are performed as part of the screening process:

- Informed consent process
- History and physical
- Cardiovascular and medical exam
- Pregnancy testing for women of childbearing age
- 12-lead ECG
- TOE (optional if a TOE is performed on the day of procedure)
- Modified Rankin Scale
- Medication assessment
- CHA2DS2-VASc score:

| CHA2DS2-VASc                                                  | Score |
|--------------------------------------------------------------------------------------------|--------------|
| Congestive heart failure/LV dysfunction                                                    | 1            |
| Hypertension                                                                               | 1            |
| Age ≥ 75                                                                                   | 2            |
| Diabetes mellitus                                                                          | 1            |
| Stroke/TIA/TE                                                                              | 2            |
| Vascular disease [prior myocardial infarction, peripheral artery disease or aortic plaque] | 1            |
| Age 65-74                                                                                  | 1            |
| Sex category [i.e. female gender]                                                          | 1            |

- HAS-BLED score:

| HAS-BLED                                                                                            | Score |
|------------------------------------------------------------------------------------------------------------|--------------|
| H ypertension history (uncontrolled, > 160 mmHg systolic)                                           | 1            |
| A bnormal renal function/renal disease (dialysis transplant, creatinine > 2.6 mg/dL or > 200μmol/L) | 1            |
| L iver disease (cirrhosis, bilirubin > 2x normal AST/ALT/AP > 3x normal)                            | 1            |
| S troke history                                                                                     | 1            |
| B leeding, anemia, or predisposition to bleeding                                                    | 1            |
| L abile INR (Unstable/high INR's, or poor time (< 60% time in therapeutic range)                    | 1            |
| E lderly - Age ≥ 65 years                                                                           | 1            |
| D rugs - Medication usage predisposing to bleeding (antiplatelet agents, NSAIDs)                    | 1            |
| A lcohol usage history (> 8 drinks/week)                                                            | 1            |

The principal investigator or delegated study personnel is responsible for screening potential subjects to determine subject eligibility for the study. Enrollment information (date of consent, inclusion/exclusion information, etc.) will be recorded in the subject's hospital records and on the Baseline and Inclusion/Exclusion eCRF. The Inclusion/Exclusion eCRF should be submitted within one week and will serve as notification of enrollment to the Sponsor upon receipt.

If a subject does not meet all inclusion criteria or meets any of the exclusion criteria, the subject cannot participate in the study. The Baseline/Screening and Inclusion/Exclusion eCRFs should be completed, in addition to the Withdrawal eCRF (consented screen failure), as applicable. If the subject was enrolled (i.e. consented and the dilator/delivery system introduced), but meets the exclusion criteria during the procedure, the Baseline, Inclusion /Exclusion, Procedure, and Withdrawal eCRFs (complete 7 days after the attempted procedure) should be completed.

Serious adverse events will be reported from the time the dilator/device delivery system has been introduced to the time the subject concludes the study. An Adverse Event eCRF should be completed, as applicable.

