#### **4.2.2 Number of study subjects**

Approximately 1000 subjects will be enrolled in the study at up to 75 sites in EMEA, ANZ, Latin America, and AP. A list of clinical investigation sites and ECs will be kept under separate cover and is available upon request (**Appendix F**).

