#### **4.3.2 Secondary objectives**

The Amulet observational post-market study has three secondary objectives:

1. Technical success – successful implantation of the Amulet device in the LAA
2. Procedural Success – technical success and the absence of major adverse events during hospitalization. Major adverse events include death, stroke, embolism, pericardial or other major bleeding requiring intervention, device embolization, and major vascular complications
3. Report percentage of subjects taking OAC and antiplatelet drugs through 2 years

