##### **4.4.2 Exclusion criteria**

Subjects are not eligible for clinical study participation if they meet any of the following six exclusion criteria:

1. Subject with evidence of an intracardiac thrombus
2. Subject with active infection or active endocarditis or other infections producing bacteremia
3. Subject where the placement of the device would interfere with any intracardiac or intravascular structures

4. Subject with any medical disorder that would interfere with completion or evaluation of clinical study results
5. Women of childbearing potential who are, or plan to become, pregnant during the time of the study (method of assessment per physician discretion)
6. Subject with LAA anatomy that does not accommodate a device per the sizing guidelines

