#### **4.5 Informed Consent Process**

The process for obtaining informed consent must comply with the ethical principles defined in the current version of the Declaration of Helsinki (**Appendix C**).

Prior to enrollment in the clinical study, all subjects will be consented, as required by applicable regulations and the site's ethics committee (EC). Informed consent must be obtained from each subject prior to the device implant procedure. The consent form must be signed and dated by the subject and by the person obtaining the consent, where applicable.

The principal investigator (PI) or his/her authorized designee will conduct the informed consent process. This process will include a verbal discussion with the subject on all aspects of the clinical study that are relevant to the subject's decision to participate, and the subject should be allowed adequate time to review and ask questions.

Documentation that informed consent was obtained will be recorded on the eCRF and in the subject's medical record. The signature date on the consent form should be referenced. The original signed informed consent should be filed in the subject's study chart and a copy of the signed consent form given to the subject per EC requirements.

A template of the informed consent form is provided in **Appendix G**. Any changes to the template must be approved by SJM prior to ethics committee review and approval.

A subject cannot be consented to the study prior to EC approval of the informed consent form. The subject shall be provided the informed consent form that is written in a language understandable to the subject and has been approved by the site's EC.

The subject is enrolled in the study when consent has been obtained and the dilator/delivery system is introduced. Failure to obtain informed consent from a subject prior to study enrollment must be reported to SJM as soon as possible and to the reviewing site's EC consistent with the site's EC reporting requirements.

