## **6.8 Subject Withdrawal**

Subjects must be informed about their right to withdraw from the study at any time and for any reason without sanction, penalty, or loss of benefits to which the subject is otherwise entitled. Withdrawal from the study will not jeopardize their future medical care or relationship with the investigator. Subjects will be asked to specify the reason for their termination, but have the right not to answer.

The investigator may decide to withdraw a subject from the study at any time with reasonable rationale. The subject's future care will not be influenced by a decision, voluntary or otherwise, to withdraw from the study. All reasonable efforts should be made to retain the subject in the study until completion of the study.

Reasons for subject withdrawal include, but are not limited to:

- Subject withdraws consent
- Subject refuses to continue their participation
- Subject does not meet the inclusion/exclusion criteria (withdraw attempt to treat subjects 7 days after the date of the attempted procedure)
- Subject is deceased (event or symptoms pertaining to outcome of death must be documented on an Adverse Event eCRF)
- Subject's participation is terminated by the PI or investigator, although the subject consented, since participation is no longer medically appropriate
- Subject is 'lost to follow up' (subject does not adhere to the scheduled follow up visits but has not explicitly requested to be withdrawn from the study)
- Site personnel should make reasonable efforts to locate and communicate with the subject in order to achieve subject compliance to the scheduled follow up visits

If a subject withdraws from the study, the site will record the subject's reasons for withdrawal on the Withdrawal eCRF.

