## **12. STATISTICAL METHODS**

No formal hypothesis will be tested for this observational post-market study. However, point estimates and exact 95% confidence intervals will be provided for the following rates in the study:

- Procedural serious adverse events (0 - 7 days) post procedure or before hospital discharge whichever latest) will be summarized for all subjects as well as stratified by imaging modality used for implanting the device (TOE and ICE)
- Late serious adverse events through 2 years
- Occurrence of ischemic stroke , systemic embolism and cardiovascular death through 2 years
- Occurrence of bleeding (including hemorrhagic stroke) events through 2 years

Data collected on the following objectives will also be reported:

- Technical success (secondary objective)
- Procedural success (secondary objective) - This objective will be summarized for all subjects as well as stratified by imaging modality used for placement of the device (TOE and ICE)
- OAC usage through 2 years (secondary objective)

- Serious Adverse Events – this may include, but is not limited to:
  - Significant bleeding events (e.g. cardiac tamponade, central nervous system (CNS) bleeding, and any bleeding related to the device or procedure that necessitates an operation)
  - Endocarditis
  - Device embolization (summarized by those that can be snared, and those that require surgical intervention)
  - Thrombus on device
  - All strokes
  - Transient ischemic attacks
  - Systemic embolism
  - Cardiovascular death
- Closure at procedure and 1-3 months post implant
  - The echo core lab's adjudication of residual flow will be used for this analysis. The following guidelines will be used:
    - None – No color flow jet in or out of the LAA
    - Small leak: < 3 mm diameter jet by color flow Doppler
    - Medium leak: 3-5 mm diameter by color flow Doppler
    - Large leak: > 5 mm diameter jet by color flow Doppler

Other variables may be summarized as deemed appropriate. The numerator for all rates will be the number of subjects who experience the corresponding event. The denominator for all rates will be subjects who experience the corresponding event plus all other subjects who achieve 2-years of follow-up.

Version 9.0 or higher of the SAS® statistical software package or other widely accepted statistical software will be used to provide all statistical analyses. Unless otherwise stated, attempts will not be made to adjust for multiple comparisons.

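### Section 12's 2-year denominator drops failed implant attempts that are withdrawn at day 7, so technical and procedural success can be overstated

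*Protocol*

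**What the plan says.** Section 4.5 fixes enrolment at the start of the attempt: "The subject is enrolled in the study when consent has been obtained and the dilator/delivery system is introduced".

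Section 6.1 then provides for an enrolled subject who "meets the exclusion criteria during the procedure". Baseline, Inclusion/Exclusion, Procedure and Withdrawal forms are completed, the last of these 7 days after the attempt. Section 6.8 lists the matching withdrawal reason: "Subject does not meet the inclusion/exclusion criteria (withdraw attempt to treat subjects 7 days after the date of the attempted procedure". Neither section names the criteria concerned. One that could plausibly come to light during an attempt is exclusion 6 in Section 4.4.2: "Subject with LAA anatomy that does not accommodate a device per the sizing guidelines".

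Section 4.3.2 defines the first secondary objective as "Technical success – successful implantation of the Amulet device in the LAA". Procedural success is technical success without an in-hospital major adverse event.

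Section 12 lists both among the outcomes to be reported, with procedural success also broken down by TOE and ICE guidance. After those lists it states: "The denominator for all rates will be subjects who experience the corresponding event plus all other subjects who achieve 2-years of follow-up". No other denominator is given for the two success outcomes.

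**The concern.** Technical success is settled at the procedure and procedural success by hospital discharge. The Section 12 denominator asks instead whether a subject without the event was followed for 2 years. For an adverse event, the subjects affected by that condition are the event-free ones. For a success outcome the roles are reversed: every success stays in, and a failure stays in only if the subject reaches 2 years.

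The protocol also contains a rule that ends follow-up at day 7 for some failed attempts. The two provisions together remove failures and never successes, so any bias from them is upward. Two of the three secondary objectives are affected, as is the TOE/ICE breakdown of procedural success. Nothing ensures that the bias is the same under both imaging methods.

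**Working it through.** **Inputs.** The protocol gives a planned size ("Approximately 1000 subjects will be enrolled in the study at up to 75 sites") but no expected success rate, number of failed implants or share withdrawn. There is therefore no figure of the plan's own to reproduce. Assumed here: N = 1000 enrolled, F = 20 or 50 failed implants, and none, half or all of them withdrawn at day 7. Failed implants that are not withdrawn are taken to reach 2 years.

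**Technical success.** Let S = N − F be the successful implants and k the failed implants that do not reach 2 years.

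- Section 12 rule: S / (S + F − k)
- All enrolled: S / (S + F)

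| F | k | Section 12 rule | All enrolled |
|---|---|---|---|
| 20 | 0 | 980/1000 = 98.0% | 980/1000 = 98.0% |
| 20 | 10 | 980/990 = 99.0% | 98.0% |
| 20 | 20 | 980/980 = 100% | 98.0% |
| 50 | 0 | 950/1000 = 95.0% | 950/1000 = 95.0% |
| 50 | 25 | 950/975 = 97.4% | 95.0% |
| 50 | 50 | 950/950 = 100% | 95.0% |

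The two columns agree only when k = 0. Each failure lost raises the reported rate. When k = F the reported rate is 100% whatever the number of failures.

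**Procedural success.** Let M be the implanted subjects with an in-hospital major adverse event, L those among them who do not reach 2 years, and P = S − M the procedural successes.

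- Section 12 rule: P / (P + M − L + F − k)
- All enrolled: P / N

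Assume F = 20, all withdrawn (k = 20), and M = 30, so P = 980 − 30 = 950.

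- L = 0, only the failed implants lost: 950/(950 + 30) = 950/980 = 96.9%, against 950/1000 = 95.0%.
- L = 7: 950/(950 + 23) = 950/973 = 97.6%, against 95.0%.

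With F = 50, k = 50, M = 30 and L = 0, P = 920: 920/950 = 96.8%, against 920/1000 = 92.0%.

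Procedural success stays below 100% in these examples because subjects with an in-hospital event who survive and reach 2 years remain in the denominator as failures.

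**The case against.** The best defence is that the denominator sentence was never meant for these outcomes. Section 12 speaks of rates when introducing the four primary items, refers to subjects who experience an event, and puts technical and procedural success in a second list of data to be reported. That list also holds closure at the procedure and at 1 to 3 months, for which a 2-year condition makes little sense. This makes the intended reach of the sentence arguable. It does not remove the problem: the sentence covers all rates without exception, follows both lists, and has no alternative beside it.

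Second, withdrawal alone removes nobody from the analysis. Section 6.1 still calls these subjects enrolled and requires a Procedure form for them. That is correct. The inflation comes from the Section 12 denominator, and the day-7 rule matters because it guarantees that these subjects miss 2 years.

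Third, the outcomes are secondary and descriptive: "No formal hypothesis will be tested for this observational post-market study". That limits the consequence but does not make the estimate right.

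Three stronger readings are tempting and are not supported:

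- A reader might infer that technical success must come out at 100%. That needs every failed implant to be withdrawn or otherwise miss 2 years. Sections 6.1 and 6.8 tie day-7 withdrawal to unmet eligibility criteria. An attempt that fails for another reason has no clear day-7 rule, and Section 6.8 asks sites to make reasonable efforts to retain subjects. The withdrawal reason in Section 6.8 could be read as covering all attempts, and Section 6 ties the form schedule to enrolled subjects who receive the device. On that reading 100% would follow, but it is only one reading.
- A reader might infer that a confidence interval will exclude the true value. Section 12 promises exact 95% intervals for the four primary rates only and none for the success outcomes.
- A reader might infer that any failed implant is by definition an exclusion under criterion 3 or 6. Section 6.1 names no criteria, intracardiac thrombus (criterion 1) could apply equally, and a device that seats badly does not automatically breach the sizing guidelines.

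**Conclusion.** The point holds as a denominator error. Applied as written, Section 12 removes from technical and procedural success every enrolled subject whose attempt fails and who is withdrawn at day 7, and so biases both upward. For 1000 enrolled, reported technical success lies between 98.0% and 100% with 20 failures (98.0% over all enrolled) and between 95.0% and 100% with 50 failures (95.0% over all enrolled), depending on the share withdrawn. The 100% is an upper limit. Procedural success rises by about 2 points in the 20-failure example (96.9% against 95.0%).

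The direction rests on the literal reach of the denominator sentence and on at least one failed implant being withdrawn or otherwise missing 2 years. The sizes rest on assumed numbers of failures, withdrawals and in-hospital events, none of which the protocol gives.

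**What to change.** In Section 12, exempt technical and procedural success from the 2-year denominator. State that both, including the TOE/ICE breakdown of procedural success, are reported over all enrolled subjects as Section 4.5 defines enrolment, whatever the later eligibility finding, withdrawal or length of follow-up. State that any attempt without implantation counts as a failure of both outcomes, and report the reasons for non-implantation descriptively.

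No change is needed to when eligibility may be judged. The denominator statement is enough, because the outcome then no longer depends on the eligibility finding.

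The cost is a few sentences. Section 6.1 already requires the Procedure and Withdrawal forms for subjects excluded during the procedure, and Section 6.8 has sites record withdrawal reasons. The case report forms are kept under separate cover (Appendix H), so whether the Procedure form has a field for the reason of non-implantation needs checking. The downside is slightly lower reported success rates.

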## **6.2 Implant/Procedure/Post-Procedure**

After the subject has met preliminary inclusion criteria, the implant procedure can be scheduled.

The baseline TOE is optional if a TOE is performed on the day of procedure to rule out the presence of intracardiac thrombus (including left atrial appendage thrombus) and to assess size and shape of the LAA.

See the IFU for procedural and post-procedural instructions.

The post-procedure care should involve the following (refer also to **Table 2**):

- Perform a TTE prior to discharge to ensure the device is positioned correctly and no pericardial effusion is present
- Aspirin (or an alternate antiplatelet) is recommended for subjects 6 months post implant
- Clopidogrel (or an alternate antiplatelet) is recommended for implanted subjects and prescription should follow standard of care
- Appropriate endocarditis prophylaxis is recommended
- Instruct the subject on when to seek medical attention
- Provide routine standard of care follow-up, including echocardiography, for evaluation of residual shunt (flow) and adverse events (including thrombus formation)
- Go to [www.amplatzer.net/device-registration-international.html](http://www.amplatzer.net/device-registration-international.html) to print the temporary subject identification card. Complete this card and provide it to the subject

